## Abstract

**Background:**

Perinatal depression and anxiety (PDA) is prevalent in new and expectant mothers, affecting millions of women worldwide. Those with a history of mood and anxiety disorders are at the greatest risk of experiencing PDA in a subsequent pregnancy. Current safety concerns with pharmacological treatments have led to a greater need for adjunctive treatment options for PDA. Changes in the composition of the microbiome have been associated with various diseases during pregnancy, and these changes are thought to play some role in perinatal mood disorders. While the relationship between PDA and the microbiome has not been explored, evidence suggests that nutritional interventions with fiber, fish oils, and probiotics may play a favorable role in neuropsychiatric outcomes during and after pregnancy. The primary objective of the present study is to assess the feasibility and acceptability of a combination of nonpharmacological interventions to maintain stability in pregnant women who have a history of depression and/or anxiety. This study will also aim to understand ease of recruitment and protocol adherence in this cohort.

**Methods:**

This is a single-centered, partially randomized, placebo-controlled, double-blind feasibility trial. One hundred pregnant women with a history of depression and/or anxiety/PDA will be recruited and randomized into one of four arms, which could include the following: receiving a daily dose of both investigational products and dietary counseling on increasing dietary fiber, receiving a daily dose of both investigational drugs only, receiving fish oil investigational product and placebo, and a control arm with no intervention. The study involves six study visits, all of which can be conducted virtually every 3 months from the time of enrollment. At all study visits, information on diet, mental health, physical activity, and sleep quality will be collected. Additionally, all participants will provide a stool sample at each visit.

**Discussion:**

It is anticipated that pregnant women with a history of depression and anxiety will be particularly interested in partaking in this trial, resulting in favorable recruitment rates. Given the positive findings of omega-3 fatty acids (O3FAs) and probiotic supplements on mental health symptoms in nonpregnant adults, we expect a similar trend in PDA symptoms, with a low likelihood of adverse events. This study will build the foundation for larger powered studies to further contribute evidence for the efficacy of this potential preventative treatment option.

**Trial registration:**

This trial was registered at ClinicalTrials/gov on October 6, 2023; NCT06074250. Trial Sponsor: The Canadian College of Naturopathic Medicine, [name], [contact].

## Background

Perinatal depression and anxiety (PDA) is prevalent in new and expectant mothers, affecting millions of women worldwide. Recent evidence suggests that one in seven women in the 20th–28th week of gestation develop depression, which impacts their ability to return to normal functioning; in the same period of gestation, anxiety has a prevalence of about 8.5%–10.5% (1). A recent meta-analysis included nine studies, with a total of 4,449 participants, examining prevalence rates of generalized anxiety disorder throughout pregnancy. Studies took place in Germany, Brazil, Italy, the UK, Turkey, Nigeria, France, and Sweden. Prevalence rates were found to range from 0.9% to 22.7%, with pooled data analysis revealing an overall prevalence of 3% (2). The pooled prevalence of antenatal depression reported in a 2021 meta-analysis of 173 studies published before 2019 was 20.7% (3). Well-known risk factors for perinatal depression include poor social support, chronic and persistent health issues in their infant, an abusive partner, marital difficulties, familial history, a history of violence, and other negative life events (4). The strongest predictor of perinatal depression, however, is a history of mood or anxiety disorders (4). Those with a history of depression have a 20-fold higher risk of a subsequent pregnancy (5), and relapse rates of 40% have been observed (4). Risk factors for new-onset perinatal anxiety can include low education, living with extended family members, a family history of psychiatric disorders, a history of sleep disorders, multiparity, and other negative life events. However, the most significant risk factor for worsening perinatal anxiety was having a comorbid psychiatric disorder, such as depression (6). Available treatment options for these disorders in the peripartum population include pharmacotherapy and psychotherapy. However, safety concerns for pharmacological treatments during pregnancy and lactation, limited access to care for psychotherapy, and the stigma of mental illness are major barriers to implementing these treatment options (7). Moreover, lack of treatment is associated with morbidity for the mother, infant, and family system and impairment in quality of life (7). Acceptable and readily available treatment alternatives are urgently required.

There is emerging evidence that the gut–brain axis (GBA) is a reasonable target for the management of PDA disorders. The GBA is a recently realized phenomenon in medicine, suggesting continuous bidirectional communication between the gut microbial community and the brain, a requirement for achieving and maintaining gastrointestinal homeostasis and cognitive function. Dysbiosis—an imbalance in bacterial composition—has been implicated in many disorders, including mental health (8). Thus, optimizing the health of the gut microbiome (i.e., treating dysbiosis) may be a logical approach to preventing and treating mood disorders.

Pregnancy itself has been associated with changes in the gut microbiome driven by immunological, hormonal, and metabolic changes—these changes are proinflammatory in nature, leading to an increase in cytokines and leukocytes and the recruitment of other immune cells (macrophages, natural killer cells, etc.) that aid in angiogenesis, transport of respiratory gases and nutrients between mother and fetus, and protection against pathogens (9). Interestingly, certain changes in the composition of the microbiome have been associated with various diseases during pregnancy, such as gestational diabetes, preeclampsia, fetal growth restriction, and obesity (9). Likewise, these changes are thought to be at least partially at play in perinatal mood disorders. A 2022 mini-review examined the correlation between perinatal depression and dysbiosis of the mother’s microbiome and reported dysbiosis as a likely precipitating factor in the development of psychiatric disorders during pregnancy (10). Emerging evidence suggests that nutritional interventions, with fish oils, probiotics, and prebiotics may play a favorable role in neuropsychiatric outcomes (11–16) and that some of these effects are mediated at least partially, by restoring eubiosis.

While not yet examined in a pregnant population, the protective effects of specific nutrients and diets have been demonstrated in major depressive disorder (MDD) in nonpregnant adults. For example, the onset of depression has been shown to increase with high-fat Western diets and significantly decrease with Mediterranean diets (8). The latter has demonstrated a reduction in oxidative stress and an increase in neurotransmitters serotonin, noradrenalin, dopamine, and monoamines, all of which play a role in major depression (8). The higher intake of plant-based fiber and omega-3 fatty acids (O3FAs) in Mediterranean diets may partly be responsible for this protective effect. Dietary fiber is fermented by cecum and large-intestine bacteria. In addition to changing the abundance of specific strains of bacteria, it also drives the levels of short-chain fatty acid production (17). Several observational studies have linked fiber intake to a reduction in the severity of depression as well as depression onset. Mechanisms proposed for this outcome include increases in levels of certain neurotransmitters, neurotrophic factors (e.g., brain-derived neurotrophic factor), and reductions in inflammatory biomarkers (17).

Specifically in the pregnant population, a recent retrospective cohort analysis examined the results of three studies (a randomized controlled trial of a low-glycemic-index diet in pregnancy, the pregnancy exercises and nutrition research study, and a randomized controlled trial on probiotics). Together, data from 1,521 participants were included in this analysis, which showed that the average daily intake of fiber was statistically significant with regard to maternal well-being (*r* = 0.13; *p* < 0.01). Results indicated that nutrients in whole grains, fruits, and vegetables were associated with improved mental health, and the authors suggested that the high fiber content in such foods is the source of these observed benefits (18).

Multiple randomized controlled trials (RCTs) have investigated probiotics in pregnancy. In 2017, Slykerman et al. reported significantly lower postpartum depression and anxiety scores in women taking probiotics versus placebo (19). However, this analysis was done retrospectively as a secondary outcome. A 2020 RCT by Dawe et al. found no impact on psychiatric outcomes of obese women at 26 weeks of gestation. However, this sample had lower baseline mental illness scores than what would have been expected, and there was no postpartum assessment (20). In 2021, Browne et al. completed a pilot RCT and concluded that the impact of probiotics on prenatal maternal anxiety and depression is feasible and acceptable. While depression and anxiety symptoms decreased after the intervention, the authors found no significant difference compared to placebo and concluded that the small sample size (*n* = 40) may have underpowered the design (21).

Recent evidence points to O3FAs having an impact on the composition of the microbiome. In rodent models, maternally separated rats with increased stress markers have an altered composition of bacteria in their microbiome, including decreased numbers of bacteria in the *Lactobacillus* genus and elevated numbers of *Oscillibacter*, *Anaerotruncus*, and *Peptococcus* general (22). Pusceddu et al. showed that with long-term administration of eicosapentaenoic acid (EPA)/docosahexaenoic acid (DHA) in stressed rodents, there is a restoration of the microbiome composition and reduction of inflammatory processes typically associated with stress (23). Specifically, EPA/DHA supplementation appeared to restore the microbiome composition to a state similar to that of nonstressed rodents, including increased *Lactobacillus* genus and reduced *Anaerotruncus* genus (23).

Currently, data linking O3FA administration with benefits in mood disorders through microbiota modulation is mostly limited to rodent models. However, the positive findings from observational and clinical trials on the impact of O3FAs on mood disorders call for a closer look at the interaction of fish oil with the microbiome and its impact on the GBA of pregnant women (24).

### Rationale for study

Evidence for the positive role of fiber, probiotics, and O3FAs in depression and anxiety is accumulating. Studies on the combination of these supplements and their mitigating effects on the microbiome remain elusive. A significant knowledge gap remains on the usability and efficacy of fiber, probiotics, and O3FAs in the pregnant population, particularly in relation to mental health disorders. Moreover, challenges exist in the design and conduct of randomized controlled trials in pregnancy or the use of complex, combination interventions, making drawing inferences challenging. Given the nonpharmacological nature of the supplements and their wide availability, safety, and cost-effectiveness, they have a high potential to serve as a preferred management option for the prevention or treatment of mental health disease in pregnant and lactating mothers. Demonstrating the relationship in this population is the first step in using an appropriate research design.

### Objectives

The main objective of this study is to assess the feasibility and acceptability of a combination of nonpharmacological interventions—a high-fiber diet, probiotics, and fish oil supplementation—in currently stable pregnant women with a history of depression and or anxiety. This population has specifically been chosen because a history of mood or anxiety disorders is the strongest predictor of PDA (4).

This study will also aim to understand the ease of recruitment, protocol adherence, and treatment compliance in this cohort. The findings of these objectives will inform on strategies needed to build a larger trial aimed at comparing the efficacy of these interventions and the magnitude of change and impact of the microbiome and PDA.

## Methods

### Trial design and setting

This is a single-centered, partially randomized placebo-controlled double-blind feasibility trial with three intervention arms (Gutopia, Gutboost, and Gutless) and one active control. In total, 100 pregnant women with a history of depression and/or anxiety/PDA attending Sunnybrook Hospital Clinics in the Greater Toronto Area will be recruited.

Participants in Gutopia will receive a daily dose of both investigational products and dietary counseling on increasing dietary fiber. Participants in Gutboost will receive a daily dose of both investigational supplements, while participants in the Gutless arm will receive fish oil and a placebo. Participants in Gutless and Gutboost will be blinded to the status of the placebo/probiotic they will be receiving. The study member interacting with the patients will also be blinded to the treatment group the participant is assigned to. Participants who fully consent to receiving both investigational products, including placebo, will be fully randomized to one of the intervention arms. Participants not willing or able to take a placebo or probiotics will be assigned (not randomized) to the appropriate group that accommodates their preferences/needs. Participants unable or unwilling to take any of our investigational products will be assigned to the active control arm. Women in the control arm will receive standard care offered to all obstetric patients seen at the hospital.

The study involves six study visits, all of which can be conducted virtually every 3 months from the time of enrollment (**Figure 1**). The last study visit will happen between 9 and 12 months postpartum. Two of the study visits will occur during pregnancy [enrollment (visit 1) and third trimester (visit 2)], with the remaining occurring at 1, 3, 6, and 9 months postpartum. At all study visits, information on diet, mental health, physical activity, and sleep quality will be collected. Additionally, all participants will provide a stool sample at each visit, using our stool collection kits, which will be shipped to or dropped off at our center.

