### Randomization and baseline evaluation

All eligible patients interested in participating will be consented to and randomized or assigned to an intervention or control arm based on responses during screening. If eligible for full randomization, this will be completed by the study principal investigator using a computer-generated randomization via random permuted blocks. The study coordinator will only be informed of the status of randomization to the Gutopia arm and will be blinded to the Gutboost and Gutless arms.

Once randomized, the participant will be scheduled for the baseline assessment as soon as possible. If scheduled as a virtual visit, a stool kit will be mailed to the participant or provided at their prenatal visit. There is no predetermined time between the screening and baseline; however, the baseline visit will take place prior to the 35th gestational week (visit 2). The collection of baseline questionnaires will include the following: The Generalized Anxiety Disorder-7 (GAD-7), The Edinburgh Postnatal Depression Scale (EPDS), Single-Item Sleep Quality Scale, Pregnancy Physical Activity Questionnaire Consumer Financial Protection Bureau—Financial Wellbeing (CFPB-FWB), Demographic Questionnaire, and the Dietary Screening Form. Please see the supplementary materials for a breakdown of the versions used and the psychometric properties of each questionnaire. The baseline visit will also include the provision of a stool sample.

There will be a total of six study visits; visit 1 (baseline) and visit 2 will occur during pregnancy, with the remaining four scheduled to take place in the postpartum period (**Figure 1**). All questionnaires completed at baseline, with the exception of the CFBP-FWB, the Demographic Questionnaire, and the Dietary Screening Form, will be completed at all postpartum visits. A postdelivery questionnaire will be completed at visit 3 (~ 4–6 weeks postpartum), and a postpartum questionnaire will be completed at visits 4–6. The sessions will be 45–60 minutes in length.

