## Discussion

Given the prevalence of PDA and its resulting impact on quality of life and infant well-being, the importance of investigating underutilized and overlooked nonpharmacological options is paramount. Specifically, the need to investigate alternative approaches in comparison to prescription medication and psychotherapy has been identified as an important need by expecting and new mothers. It is anticipated that pregnant women with a history of depression and anxiety will be particularly interested in partaking in this trial, resulting in favorable recruitment rates. Given the positive findings of O3FA and probiotic supplements on mental health symptoms in nonpregnant adults, we expect a similar trend in PDA symptoms, with a low likelihood of adverse events.

While not our main objective, we anticipate a correlation between the microbial composition and probiotics and O3FA supplementation. As several recent studies have demonstrated a positive impact of probiotics (19–21) or O3FAs (22, 23) on mental health outcomes via changes in the gut microbiome, this has yet to be demonstrated in individuals at risk of PDA. Having intervention groups that provide both supplements (Gutboost) versus O3FA alone (Gutless) will allow us to determine potential interaction between these supplements. We anticipate a difference in mental health scores between the Gutboost and Gutless intervention groups. Incorporating a third intervention arm where dietary counseling is provided in addition to supplementation (Gutopia) further allows us to understand the interaction between diet and supplementation. We anticipate differences in mental health scores between Gutopia compared to the other intervention arms. Additionally, having an active control arm can potentially inform the magnitude and directionality of these changes by comparing outcomes in the intervention arms (*N* = 75) to the active control arm (*N* = 25).

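### The placebo-controlled, double-blind label holds only for Gutboost versus Gutless among women randomised to those arms, and the two statements on staff blinding do not fit together

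*Protocol article*

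**What the plan says.** The abstract calls the study a "partially randomized, placebo-controlled, double-blind feasibility trial". The section Trial design and setting repeats this for all arms: "This is a single-centered, partially randomized placebo-controlled double-blind feasibility trial with three intervention arms (Gutopia, Gutboost, and Gutless) and one active control".

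The same section then describes blinding more narrowly for participants: "Participants in Gutless and Gutboost will be blinded to the status of the placebo/probiotic they will be receiving". It follows directly with a sentence on staff that carries no such limit: "The study member interacting with the patients will also be blinded to the treatment group the participant is assigned to". It also allows allocation by preference: "Participants not willing or able to take a placebo or probiotics will be assigned (not randomized) to the appropriate group".

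The section Randomization and baseline evaluation describes what the coordinator knows of the arms: "The study coordinator will only be informed of the status of randomization to the Gutopia arm and will be blinded to the Gutboost and Gutless".

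On use of the mood scores, the section Mental health outcome plans between-group analyses of EPDS and GAD-7. The Discussion expects a Gutboost versus Gutless difference and adds: "We anticipate differences in mental health scores between Gutopia compared to the other intervention arms". It also intends to set the intervention arms (N = 75) against control (N = 25).

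**The concern.** A trial-wide claim of placebo control and double-blinding tells the reader that expectation is balanced across every comparison. Here it is balanced across one. EPDS and GAD-7 are completed by the women themselves, so a woman who knows her arm is an unblinded assessor of her own outcome. Gutopia women also receive weekly supportive contact, so attention is mixed with treatment. Expectation and attention alone could produce the differences that the Discussion anticipates for Gutopia, and could contribute to those against control.

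The staff sentence is a second and separate problem. If it is taken at its word, nobody in contact with participants knows any allocation. Other sections of the article rule that out for Gutopia.

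**Working it through.** No power or sample-size figure is involved, so there is nothing of that kind to reproduce. The check classifies the arms, counts the contrasts, and sets the staff statements side by side.

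**Step 1. What each arm receives and what its participants can know** (from Trial design and setting, The intervention, and Investigational products)

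| Arm | Fish oil | Capsule | Diet counselling | How filled | Participant blinded |
|---|---|---|---|---|---|
| Gutopia | active | probiotic | yes, open | randomised, or by preference | no |
| Gutboost | active | probiotic | no | randomised, or by preference | yes, if randomised |
| Gutless | active | placebo | no | randomised, or by preference | yes, if randomised |
| Control | none | none | no | by refusal or inability | no |

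Fish oil and diet have no placebo. The placebo capsule separates one pair only, Gutboost and Gutless.

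**Step 2. All pairwise contrasts.** Four arms give 4 × 3 / 2 = 6.

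| Contrast | Both arms open to randomisation | Participants blinded in both |
|---|---|---|
| Gutboost – Gutless | yes | yes |
| Gutopia – Gutboost | yes | no |
| Gutopia – Gutless | yes | no |
| Gutopia – Control | no | no |
| Gutboost – Control | no | no |
| Gutless – Control | no | no |

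Blinded: 1 of 6. Unblinded: 5 of 6, of which 3 are also non-randomised.

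**Step 3. Only the comparisons named in the Discussion.** Gutboost versus Gutless (1), Gutopia versus each of the other two intervention arms (2), and pooled intervention versus control (1) make 4. Unblinded: 4 − 1 = 3 of 4.

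**Step 4. How many women the blinded contrast can hold.** 75 + 25 = 100. Block sizes of three and six are consistent with equal allocation to three arms. On that assumption 75 / 3 = 25 per arm, so at most 2 × 25 = 50 of 100 women are in the blinded contrast. This is an upper limit. A woman who declines placebo can only be put in an arm with the active capsule. A woman who takes fish oil but declines the probiotic fits only Gutless among the intervention arms. Either can work out her product from her own stated preference. The article gives no figure for how many such women are expected, so the reduction below 50 cannot be calculated.

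**Step 5. Staff blinding, side by side.**

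- Trial design and setting: the patient-facing study member is blinded to treatment group, with no exception.
- Randomization and baseline evaluation: the coordinator is told who is in Gutopia and is blind only between the other two intervention arms.
- The intervention: a trained team member contacts Gutopia women weekly and checks how far they follow the dietitian's advice.
- Outcomes measured: the Gutopia fibre target is followed up by frequent phone calls.

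Whoever makes these diet contacts is dealing with participants and must know that they are in Gutopia. The unqualified statement therefore cannot be true of all patient-facing staff, whether or not the coordinator is one of them.

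**Step 6. Whether other blinding protects mood scores.** The article also blinds the researchers who analyse stool and the person who double-checks laboratory data. Neither affects a questionnaire that the woman fills in herself.

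**The case against.** The strongest reply is that the article discloses the limit. Soon after the label, it confines participant blinding to Gutless and Gutboost, and it never claims that Gutopia or control women are blinded. This stands. It reduces the fault to a headline label wider than the design beneath it, and does not remove it, because the abstract carries the label without the limit.

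Second, the staff sentence follows the one about Gutless and Gutboost and contains the word also, so it may have been meant for that pair only. The randomisation section would then be an elaboration. That reading is possible, but the sentence speaks of treatment group without restriction and needs the limit written in.

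Third, mood is not the primary outcome. Process evaluation is, and the analysis of covariance with mental health as primary outcome applies only if recruitment continues into a larger trial. This stands and limits the weight of the point. The between-group EPDS and GAD-7 comparisons are, however, planned for this trial too.

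Fourth, an analysis plan that is not shown might define the randomised set. It might, and its absence here is not the fault. The article as it stands compares by group without separating randomised from preference-placed women.

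A reader might also go further than the text allows:

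- One might call the whole trial open-label. That would be as inaccurate as double-blind: there is a matching placebo capsule and participant blinding in two of four arms.
- One might conclude that the mood comparisons are unblinded because the coordinator knows Gutopia status. The openness comes from what the arms receive.
- One might treat the coordinator and the patient-facing study member as the same person. The article does not say so.
- One might say that preference-placed women are told their product. The article says nothing on this; they can infer it.
- One might say that Gutopia or control results will be reported as double-blind. No section says that.

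**Conclusion.** The point holds in a limited form. The label is correct for one comparison, Gutboost versus Gutless, and only among women randomised to those arms. Three of the four comparisons named in the Discussion (control pooled), or five of six pairwise, are unblinded on self-reported mood. Every contrast with control is also non-randomised. At most 50 of 100 women are in the blinded comparison, assuming 25 per arm, and fewer to the extent that women are placed by preference. The counts rest on the arm descriptions alone; only the 50 depends on the equal-allocation assumption.

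The staff-blinding statement is a separate inconsistency with the randomisation section and the Gutopia diet follow-up.

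The feasibility outcomes do not depend on the label. The point is worth correcting now because the article intends, if the trial succeeds, to keep enrolling towards an efficacy trial with mental health scores as primary outcome. The label and the mixed comparison groups would then carry forward.

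**What to change.** 1. Describe the trial in the abstract and the design section as partially blinded, with a placebo-controlled, double-blind comparison limited to women randomised to Gutboost or Gutless.
2. Run the probiotic comparison of EPDS and GAD-7 in that randomised set, and report preference-placed women separately.
3. Label every contrast involving Gutopia or control as unblinded and not placebo-controlled, and those with control as non-randomised as well.
4. Reconcile the staff sentence in Trial design and setting with Randomization and baseline evaluation by limiting it to Gutboost versus Gutless.

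The cost is a change of wording and the definition of one analysis set. The set for the probiotic comparison becomes somewhat smaller, by an amount the article does not let one estimate, and the design label becomes less favourable. Nothing in treatment or data collection changes.
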